# Study on awareness and management based health action using video intervention (SAMBHAV) for postpartum depression among mothers attending immunisation clinic in a tertiary medical college hospital: Study protocol

**DOI:** 10.1371/journal.pone.0301357

**Published:** 2024-04-03

## Abstract

**Introduction:**

Pregnancy exerts a detrimental effect on women’s mental health. Maternal mental health is considered as one of the public health concerns as it impacts the health of both mother and the child. One in five people in developing countries experience serious mental health issues during pregnancy and after giving birth. In India, postpartum depression (PPD) affects 22% of women, according to a research by WHO. The available data on mental health literacy among women, showed that only 50.7% of the postpartum mothers who were attending paediatric tertiary care centres had adequate knowledge about PPD. It is crucial to diagnose early and adequately manage postpartum depression to avoid long-term consequences. It is also essential to seek help and utilise the available resources and services to avoid worsening of the condition and to aid in the recovery. This demonstrates the need to promote awareness, improve help seeking, reduce stigma and treatment gap associated with PPD through educational video intervention specific to cultural context and beliefs.

**Materials and methods:**

This is a quasi-experimental study without a control group that attempts to improve the awareness among the mothers about postpartum depression to understand better about the condition and also its management through video intervention. The video intervention will be developed in regional language specific to the cultural context of the setting. The video script will be finalised from the findings of the available literature and also through focus group discussion among mothers and health care professionals which will be analysed qualitatively using thematic identification. The study will use a standardized Postpartum Depression Literacy Scale (PoDLIS) which will be quantitatively analysed using paired t test before and after the intervention. Repeated measures of ANOVA will also be used to analyse the changes in literacy scale scores with respect to socio demographic variables. The mothers will also be screened for PPD using Patient Health Questionnaire 9 (PHQ 9) and feedback will be collected and analysed to find the overall usefulness of video.

**Discussion:**

If it becomes apparent that this video intervention is successful in raising awareness of PPD among postpartum mothers and reducing stigma, it can be used to aid early identification of mothers with PPD which can result in early management and improved health outcome for both mothers and children. The major goals of the video intervention are to raise awareness, lessen stigma, and prevent PPD through strong family support, adopting healthy lifestyles, having access to information, practising self-care, and enhancing help-seeking.

**Trial registration:**

The trial is registered under the Clinical Trial Registry- India (CTRI) (CTRI/2023/03/050836). The current study adheres to the SPIRIT Guidelines [See S1 Checklist: SPIRIT Guidelines].

## Introduction

During pregnancy, a woman undergoes several physical, emotional, hormonal, and psychological changes [1]. The mother’s world both familial and interpersonal undergoes enormous transformation. A mother may feel a range of emotions after giving birth, from excitement and pleasure to grief and tears [2]. Pregnancy is the time when a female is most vulnerable to developing mental illness. Maternal Mental Health disorders includes; depression, anxiety and psychosis which can develop during pregnancy or after delivery. These illnesses can have detrimental effects on the mother, her child, her family, and society if not treated [3]. Globally around 13% of postpartum mothers and 10% of pregnant women experience a mental disorder, primarily depression [4]. According to a WHO report the prevalence of Postpartum Depression is 22% in India [5]. Only about 50.7% of the postpartum mothers attending a paediatric tertiary care centre in India had adequate knowledge on postpartum depression indicating low mental health literacy [6]. Postpartum Depression can start soon after childbirth or as a continuation of antenatal depression and needs to be treated. It is characterized by symptoms of consistent low mood, inability to bond with the baby, excessive crying, inability to sleep (insomnia) or sleeping too much, overwhelming fatigue or loss of energy, reduced interest and pleasure in activities mother used to enjoy, intense irritability and anger, fear of not being a good mother, hopelessness and thoughts of harming oneself and the baby [7, 8]. A systematic review by Daria et al. showed that the studies on knowledge about PPD showed that around 30.2–62.2% among the public could correctly identify the typical symptoms of PPD and percentage of women reporting difficulties in mother child relationship also varied widely between 5 and 77.1% [9]. Postpartum Depression places mothers at increased risk for social isolation due to a lack of energy, fatigue, and feelings of incompetence, worthlessness, and helplessness [10]. Major risk factors for Postpartum Depression include past history of psychiatric illness in mothers, financial difficulties, marital conflict, lack of support from husband, domestic violence (DV), intimate partner violence (IPV), stressful life events and poor social support [11]. The birth of a female child can also be considered a risk factor for PPD in India [12, 13], China [14] and Egypt [15].

Postpartum Depression if untreated can predispose to chronic or recurrent depression, this may affect the mother and child relationship, growth and development of the baby [16, 17]. Studies have showed that infants of depressed mothers have less expressive language and performed poorly on measures of cognitive linguistic functioning [18]. Children of mothers with postpartum depression have greater cognitive, behavioural and interpersonal problems compared with the children of non-depressed mothers [19]. Scarcity of available mental health resources, inequities in their distribution and inefficiencies in their utilization are key obstacles to optimal mental health services, especially in low resource countries [20]. The systematic review by Daria et al. mentioned that the structural, attitudinal, and knowledge-related barriers were reported for not seeking help among perinatal women. The structural barriers included cost of treatment and inability to attend appointments due to: time constraints, logistics/transportation, childcare, distance/geographic mismatch, and unavailability of providers/resources. The most common attitudinal barriers were found to be associated with stigma and shame [9, 21, 22].

A research study by Heh et al. looked at the impact of informational assistance in lowering Edinburgh Postnatal Depression Scale scores and the findings showed that providing women with adequate information on postpartum depression during the postpartum period may benefit their psychological well-being [23].

Postpartum Depression often goes undetected as there is lack of awareness regarding maternal mental health issues especially in a country like India. It is imperative to raise public awareness about postpartum depression due to its detrimental effects on both mother and child’s overall health [24]. It is also equally important to make timely diagnosis and management of Postpartum Depression to prevent long term consequences. Although pregnancy and childbirth may be the same everywhere, postpartum may be viewed and experienced rather differently by women from different cultures [25]. When considering the Indian context there is a lot of stigma associated with mental illness especially when it comes to maternal mental health. Women frequently express discomfort about getting professional help and worry about being labelled "bad mothers" if they admit having depression [26]. A study by Branquinho et al. suggested that 11.4% of the participants agreed that ‘women with postpartum depression cannot be good mothers’ and 12.1% agreed with ‘women have postpartum depression because they have unrealistic expectations about caring for a baby’ [27].

It is crucial to seek proper assistance from the available resources for preventing the PPD from worsening and also to aid in recovery. This highlights the need for initiatives to reduce stigma and encourage help-seeking behaviour [28].

A systematic review of research on video-based educational interventions for modifying health behaviours demonstrated their effectiveness across a variety of health-related topics [29]. A recent study by Chaudary L et al. indicates that the knowledge on post-natal care among pregnant women visiting district hospital for a prenatal check-up can be improved through customised social media-based health education guided by a health belief model [30]. Public educational campaigns highlighting the significance of perinatal mental health problems could counteract misconceptions and trivializing notions as suggested by Daria et al. [9].

Since there is poor awareness, wide treatment gap in lower and middle income countries and lack of interventions, the present study attempts to develop and assess a video-based educational intervention that promotes awareness on Postpartum Depression among mothers in the postpartum period. Studies have showed that the employment of video-based educational interventions improved postpartum depression symptom detection, decreased stigmatizing views, and raised knowledge of the dangers that could affect the mother and baby [31]. In addition, studies on postpartum depression and video-based therapies have also been applied to enhance mother-child interactions [32].

There are no studies available in India which focuses on development of a video based intervention for promoting awareness on PPD among mothers. And the video interventions available from other countries may not be suitable to our setting because of the diverse cultural context, risk factors, language barriers and beliefs associated with PPD in India. Hence, this study is being planned to develop and evaluate a culturally relevant video intervention to improve awareness and reduce stigma on Postpartum Depression among postpartum mothers. The developed educational video series could be utilized for mothers with focus on early identification, self-care and better management of PPD.

## Objectives

Development and evaluation of a video based educational intervention in improving the awareness and reducing stigma about Postpartum Depression among postpartum mothers.

## Methods and analysis

### Study design

This study follows Quasi- experiment single group without control design with video intervention to study the effect of video intervention in improving awareness and reduction of stigma on Postpartum Depression among postpartum mothers.

### Study participants

Postpartum mothers within 6 months after child birth attending immunization clinics in urban and rural field practice area of Ramaiah Medical College, Bangalore.

### Inclusion criteria

Postpartum mothers within 6 months after childbirth who are willing to give consent and able to understand and speak in Kannada or English.

### Exclusion criteria

Mothers diagnosed with any of the major illness or Mental Health conditions.

#### Study setting

Immunization Clinics in Urban and Rural field practice area of Ramaiah Medical College Hospital, Bangalore. As the immunisation clinics are ideal for undertaking any intervention studies among mothers, as they will be visiting these clinics for vaccination of the child.

#### Study duration

27 Months (December 2022 to February 2025).

#### Study sampling

The postpartum mothers who are attending the immunization clinic at urban and rural health centres under the medical college hospital will be selected using convenience sampling.

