#### Sample size

The sample size was calculated based on the awareness of PPD referring to the study by Lekie Dwanyen, Postpartum Depression: Novel use of Video-based interventions using G-power software version 3.1, the effect size was 0.25, at confidence level of 95% and power is 80% for which the sample size is 128 [31]. Here, in this study we will be considering 130 mothers who will be satisfying the inclusion criteria and willing to consent (Fig 1).

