### Statistical analysis

The salient findings from literature search will be summarized and findings will be included for the script. The outcomes of FGDs will be qualitatively analysed. Inductive and thematic theme identification will be done using a descriptive approach. The analysis will be done manually and the themes will be generated based on the codes from the discussion. The findings will be utilized for finalising the video script. The effectiveness of the video intervention will be quantitatively analysed using paired t test. The results will be presented as mean, SD at each time point and 95% CI of the difference between pre and post means. Repeated measures of ANOVA will be used to analyse the change in Postpartum Depression Literacy Scale scores with respect to socio-demographic variables. The prevalence of PPD among mothers will be analysed using PHQ 9.

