### Limitations of the study

The study includes a single group (intervention) and there is no control group to compare the effectiveness of video intervention. The outcome includes only the improvement in knowledge and reduction of stigma on PPD among mothers and does not include assessment of any health-related outcomes such as improved quality of life and prevention of relapse. The mothers are recruited from the immunization clinics at the urban and rural health centres attached to the medical college and not be the actual representation of the community affecting the generalisability of the study findings.

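### Convenience selection leaves the planned PHQ 9 prevalence without a defined denominator; consecutive invitation with a log would reduce the selection bias cheaply

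*Protocol article*

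**What the plan says.** Under Study sampling, the protocol article states that postpartum mothers attending the urban and rural clinics "will be selected using convenience sampling". Two eligibility rules narrow the group further. Mothers must be "willing to give consent and able to understand and speak in Kannada or English", and the exclusion criterion reads "Mothers diagnosed with any of the major illness or Mental Health conditions".

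The Statistical analysis section plans two quantitative results that depend on who is enrolled:

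- a prevalence: "The prevalence of PPD among mothers will be analysed using PHQ 9";
- the literacy gain: "The effectiveness of the video intervention will be quantitatively analysed using paired t test".

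The Study outcome section also places the PHQ 9, given before the video and again 4 to 8 weeks later, under the primary outcome. The design is a "Quasi- experiment single group without control design".

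The Limitations section addresses representativeness at one level only. It notes that "The mothers are recruited from the immunization clinics at the urban and rural health centres attached to the medical college" and that they may therefore not represent the community. It does not mention how mothers are selected among those attending a clinic, and it does not link the limitation to the prevalence.

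**The concern.** A prevalence is a proportion of a defined group. With convenience selection, the number of eligible mothers who attended, were passed over or declined is not part of the method, so the percentage cannot be referred to the clinic population. If the chance of being enrolled is related to depression, the estimate is shifted, and a confidence interval computed from 130 mothers does not show the shift.

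The relation could run either way. A depressed or hurried mother may be harder to enrol. Equally, a distressed mother may be steered towards a study about depression, or be more interested in it.

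The literacy gain is exposed in a weaker sense. If mothers differ in how much they learn from the video, the mean gain describes the mix that happened to be enrolled. The plan treats such differences as possible, since it will analyse change in the literacy score by socio-demographic variables.

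The clinic setting is a constraint of the study. Selection among mothers already in the clinic is a choice that can be changed.

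**Working it through.** **Inputs**

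- From the protocol article: planned n = 130 and calculated n = 128 (Sample size); prevalence 22%, a background figure for India attributed to a WHO report (Introduction); 6 months of data collection (timeline); post-test 4 to 8 weeks after pre-test (Data collection).
- Assumed: the true prevalence p in the clinics is 22%; r, the enrolment probability of a depressed mother divided by that of another mother, takes the values 0.5, 0.75, 1.25 and 2. The documents give no value for r.

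**1. The plan's own figure.** The Sample size section states "the effect size was 0.25, at confidence level of 95% and power is 80"%, giving 128. A two-sided paired t test at alpha 0.05 with a standardised change of 0.25 needs n = 128 (power 80.2%, noncentral t). At n = 130 the power is 80.8%. The figure reproduces, so there is no sample-size error here. How mothers are invited alters neither number. The article does not state sidedness; two-sided is assumed.

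**2. Sampling error of the prevalence.** Half-width = 1.96 × √(0.22 × 0.78 / 130) = 1.96 × 0.0363 = 0.071, or about 7.1 points.

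**3. Shift from selection.** Expected observed prevalence = p·r / (p·r + 1 − p).

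| r (assumed) | Calculation | Observed | Shift from 22% |
|---|---|---|---|
| 0.5 | 0.110 / 0.890 | 12.4% | −9.6 points |
| 0.75 | 0.165 / 0.945 | 17.5% | −4.5 points |
| 1.25 | 0.275 / 1.055 | 26.1% | +4.1 points |
| 2 | 0.440 / 1.220 | 36.1% | +14.1 points |

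At r = 0.5 or 2 the shift exceeds the 7.1-point half-width. At 0.75 or 1.25 it does not.

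**4. What consecutive invitation leaves in place.** The exclusion of diagnosed mental health conditions lowers the prevalence by itself. If a share x of cases is already diagnosed and so excluded (assumed), the prevalence among the rest is p(1 − x) / (1 − p·x).

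- x = 10%: 0.198 / 0.978 = 20.2%
- x = 25%: 0.165 / 0.945 = 17.5%
- x = 50%: 0.110 / 0.890 = 12.4%

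These values hold even with perfect consecutive enrolment.

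**5. Literacy gain.** Suppose two equal groups of mothers whose mean gains differ by D, and selection moves the mix by 20 points. The mean gain shifts by 0.20 × D. With D = 0.25 SD (assumed) this is 0.05 SD; with D = 0 it is zero.

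**6. Feasibility.** Six months is about 26 weeks. Subtracting the 4 to 8 week interval to the post-test leaves 18 to 22 weeks for enrolment. 130/22 = 5.9 and 130/18 = 7.2, so about 6 to 7 mothers a week.

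**The case against.** The strongest reply has five parts.

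- **Mechanism.** The article does not say that staff choose which mothers to approach. Convenience sampling may simply mean taking whoever attends on data-collection days, which is close to the proposed rule. This stands as a caution: the article leaves the mechanism open. It is also a reason to state the rule, because as written nothing excludes selective approach.
- **Prevalence is peripheral.** It is not in the objective and did not drive the sample size, and it gets one descriptive sentence. This stands, and it keeps the point minor. It is nevertheless a planned analysis, and the PHQ 9 is listed under the primary outcome.
- **Already conceded.** The Limitations section admits restricted generalisability. That covers clinics versus community, not selection among attenders.
- **Low-literacy mothers are provided for.** The research scholar administers the scale to mothers who cannot read, which lowers one barrier. This stands in part. The provision concerns completing the scale, not who is approached.
- **A screening log is operational detail.** An article may leave it to the full protocol. This stands: the absence of a log is not itself the point. The stated sampling method is.

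A reader might also infer that the literacy gain will be overstated because motivated mothers are easier to enrol. The documents do not support that. The gain is a within-mother change, and entry selection moves its mean only if gains differ between the mothers over- and under-enrolled; no figure shows that they do. Failure to return for the post-test is attrition, a separate matter.

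**Conclusion.** The point holds in a limited form. Convenience selection leaves the PHQ 9 prevalence without a defined denominator and open to selection bias of unknown direction and size. It also restricts to whom the mean literacy gain applies.

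The illustrative range of 12.4% to 36.1% around 22% rests on two assumptions: a background prevalence that the plan does not claim for these screened mothers, and enrolment ratios from 0.5 to 2 that the documents neither give nor exclude. It shows that the bias could exceed the 7.1-point sampling half-width, not that it will.

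Two stronger conclusions are tempting and unsupported. One is that the prevalence will come out too low: ratios above 1 are just as compatible with the text. The other is that consecutive enrolment would largely remove the bias. It would reduce the part due to selection among attenders. Clinic attendance, consent, language, the exclusion of diagnosed conditions and loss before the post-test would remain, and the missing control group, which the authors acknowledge, is untouched.

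This is a cheap improvement to the design, not an error that invalidates the main comparison.

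**What to change.** In Study sampling, replace convenience sampling with consecutive invitation: on each data-collection day, invite every eligible mother in order of arrival until that day's capacity is reached. Keep a log of the numbers eligible, approached, refused and enrolled.

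In Statistical analysis, state that the PHQ 9 prevalence will be reported against that log and described as the prevalence among enrolled clinic attenders without a prior mental health diagnosis. In the Limitations, add that selection by consent, language and day of attendance remains.

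The cost is a change of wording, a tally sheet at each clinic, and possibly slightly slower enrolment. The planned 130 mothers and the power are unchanged.

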#### Sample size

The sample size was calculated based on the awareness of PPD referring to the study by Lekie Dwanyen, Postpartum Depression: Novel use of Video-based interventions using G-power software version 3.1, the effect size was 0.25, at confidence level of 95% and power is 80% for which the sample size is 128 [31]. Here, in this study we will be considering 130 mothers who will be satisfying the inclusion criteria and willing to consent (Fig 1).

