### Data collection

The Postpartum Depression literacy scale will be used to conduct the pre and post-test among the postpartum mothers to examine the effectiveness of the video intervention in terms of improving awareness and reducing the stigma. The literacy scale is a self-report measure which will be easy to administer, however in case of mothers who are illiterate, the scale will be administered by the research scholar. The postpartum mothers visiting the Immunization Clinic will undertake the pre-test, screened for PPD and later will be made to watch the video. After watching the video, a feedback form will be provided to the mothers regarding the effectiveness of the video. The post-test will be conducted at an interval of 4–8 weeks of time after pre-test [35] to ensure knowledge retention and also the compliance for posttest, as the mothers will be visiting immunization clinics at 6, 10 and 14 weeks for vaccination of the child as part of the Universal Immunization Program [36]. Lastly the mothers will be re-screened for PPD using PHQ 9. In case a mother scores high on PHQ 9, indicating depression them they will be seen by the trained medical officer (As a part of District Mental Health Program (DMHP), all the PHCs runs ‘Manochaitanya Clinic’ on Tuesdays.) and later mothers will be referred to manochiatanya clinic for further evaluation and treatment by mental health professionals.

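### The 80% power at 130 enrolled mothers leaves room for only 2 missing post-tests, if 0.25 is the standardised mean change; the protocol should state the power as conditional on complete pairs

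*Protocol article*

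**What the plan says.** All references are to the protocol article.

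- **Sample size** gives the calculation in one sentence: "the effect size was 0.25, at confidence level of 95% and power is 80% for which the sample size is 128". It names the software and a cited video-intervention study as the source. It does not name the test, the sidedness or the type of effect size. The next sentence sets the number to be recruited: "Here, in this study we will be considering 130 mothers who will be satisfying the inclusion criteria and willing to consent". This counts eligible, consenting mothers, not mothers with both measurements. The 2 added to 128 are not explained, and no loss rate is given.
- **Study design** fixes a single group: "This study follows Quasi- experiment single group without control design with video intervention".
- **Data collection** requires a second measurement: "The post-test will be conducted at an interval of 4–8 weeks of time after pre-test". It gives compliance as one reason for that interval, because mothers come back for the child's vaccinations at 6, 10 and 14 weeks.
- **Inclusion criteria** admit mothers up to 6 months after birth.
- **Statistical analysis** fixes the test: "The effectiveness of the video intervention will be quantitatively analysed using paired t test".

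**The concern.** A paired t test uses only mothers with both scores. The sample size for such a test is therefore a number of complete pairs, whereas the 130 in the protocol is a number of consenting mothers at the start. The only gap between the two is 2 mothers, although every mother has to be measured again one to two months later.

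The vaccination visits are a sensible retention device, but they do not reach everyone who is eligible. A mother enrolled at or after the 14-week visit has no later visit on the protocol's list to bring her back, yet she can be enrolled up to 6 months after birth.

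At stake is how the result is read. If more than 2 mothers are lost, the 80% no longer describes the analysis, and a null or borderline result would be judged against a power slightly to clearly higher than the one achieved. The unlabelled effect size adds to this, because a reader cannot tell what change in PoDLiS score the trial was sized to detect.

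**Working it through.** **Inputs from the protocol article.** Effect size 0.25, 95% confidence, 80% power, calculated size 128, enrolment 130 (Sample size); single group (Study design); paired t test (Statistical analysis).

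**Assumptions.** 0.25 is dz = mean change / SD of change. The test is two-sided at 5%. The loss rates are 5%, 10% and 20%; the protocol gives none.

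**Step 1: reproduce 128.** With n complete pairs the test statistic follows a noncentral t distribution with n − 1 degrees of freedom and noncentrality dz × √n. Power is the probability that it falls beyond the two-sided 5% critical value.

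- n = 127: 0.25 × √127 = 2.817; power 79.8%
- n = 128: 0.25 × √128 = 2.828; power 80.2%
- n = 130: 0.25 × √130 = 2.850; power 80.8%

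So 128 is the smallest number of pairs that reaches 80%. A one-sided test would need 101, so the two-sided reading is the one that fits.

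**Step 2: is the paired test the only calculation that gives 128?** No. A one-way ANOVA with two groups and Cohen's f = 0.25 also gives a total of 128 (power 80.1%). The figure alone does not show which calculation was run. Only the paired test matches the single-group design.

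**Step 3: the margin.** 130 − 128 = 2 mothers, and 2/130 = 1.5%. The third loss leaves 127 pairs and takes power just below 80%.

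**Step 4: power with 130 enrolled, at assumed losses.** Pairs = 130 × (1 − loss), rounded down.

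| Assumed loss | Pairs | Power at dz = 0.25 | dz detectable with 80% power |
|---|---|---|---|
| 0% | 130 | 80.8% | 0.248 |
| 5% | 123 | 78.5% | 0.255 |
| 10% | 117 | 76.5% | 0.261 |
| 20% | 104 | 71.4% | 0.277 |

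The shortfall exceeds 2 percentage points from 9 losses (9/130 = 6.9%; 121 pairs, power 77.9%).

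**Step 5: how likely are 2 losses or fewer?** If mothers are lost independently, the number lost is binomial with n = 130. The chance of at most 2 losses is 52% at a true loss rate of 2%, 4% at 5% and about 0.01% at 10%.

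**The case against.** Four points can be made in the protocol's favour.

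**The protocol gives no loss rate.** A reader might infer that the 80% power is simply not delivered. The document does not support that. With up to 2 losses the power is at least 80%, and at 5% loss it is still 78.5%. The claim has to stay conditional. What stands is that the condition is strict and is not stated.

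**The metric is not named.** If 0.25 was Cohen's f for two equal groups, it corresponds to a standardised difference of 2 × 0.25 = 0.5 between means. Carried over to the paired test as a pre/post difference of 0.5 SD, dz = 0.5 / √(2 × (1 − r)), where r is the assumed pre/post correlation. With 91 pairs (30% loss), power is 91.6% at r = 0 (dz = 0.354), 97.9% at r = 0.3 and 99.7% at r = 0.5. On that reading none of these losses threatens 80%. This is a fair point and it limits the conclusion. It does not clear the section, because 128 would then come from a calculation for a design the trial does not have.

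**Retention is planned for.** Linking the post-test to vaccination visits is a real measure and should reduce losses. It leaves out mothers enrolled at or after the 14-week visit. The document does not say how many these will be.

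**The arithmetic is right, and an article may leave missing-data handling to the full plan.** Both are true. The point is not a miscalculation, nor the absence of a missing-data method. The article itself prints the calculated size and the enrolment number side by side, with no label saying that the first means complete pairs.

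**Conclusion.** The point holds in conditional form. For the planned paired t test, with 0.25 read as dz and a two-sided 5% level, 128 is a number of complete pairs, and the 80% power holds only if no more than 2 of 130 mothers miss the post-test. At assumed losses of 5% to 20%, power is 78.5% to 71.4%, and the detectable dz is 0.255 to 0.277. The shortfall is small at 5% and becomes material from about 10%.

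This rests on the dz reading, which the single-group design makes the natural one but which the document does not confirm, and on loss rates that are assumptions. It supports a correction of the stated power that should be made. It does not show that the trial is underpowered or must be enlarged.

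**What to change.** In the Sample size section:

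1. Name the test and its sidedness, and say what 0.25 is. If it is dz, define it as mean change divided by the SD of change in PoDLiS score. If it was f from a two-group calculation, redo the calculation for the paired test.
2. If dz is confirmed, say that 128 is the number of mothers with both PoDLiS scores.
3. Give an expected loss rate, taking account of mothers enrolled at or after the 14-week visit.
4. Restate power and detectable effect for the pairs expected from 130 enrolled.

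Possible wording, once dz is confirmed: *128 mothers with both PoDLiS scores give 80% power for dz = 0.25 (paired t test, two-sided 5%). With 130 enrolled this allows for 2 losses. At an expected loss of x%, the power is y% and the detectable dz is z.* At 10% loss, y and z are 76.5% and 0.261; at 20%, they are 71.4% and 0.277.

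The cost is a few sentences and a slightly less favourable power figure. Extra enrolment is not required. If the sponsor prefers to keep 80%, enrolment would be 128 / (1 − loss), rounded up: 135 at 5%, 143 at 10% and 160 at 20%.

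A linear mixed model using all 130 mothers is optional. It should not be presented as restoring power: with only two time points, a mother who has just the pre-test adds almost nothing about change.
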